### Blinding

Outcome measures will be assessed by trained assessors who will be blinded for group allocation before and after the programs. However, participants and exercise instructors will not be blinded because of the difficulty in blinding either of these in trials of specific PA/exercise modalities such as PW
[55].

### Outcome measures

Outcome measures will be assessed before commencing the program and at a follow-up testing session one week after the end of the program. The primary outcome measures are selected physical function items of the Seniors Fitness Test (30 second chair stand, 30 second arm curl, timed up and go test, and 6 minute walk test) and grip strength
[54]. Secondary outcome measures are behaviour (PA levels and sitting time), and wellbeing (joint pain, quality of life, vitality).

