**Methods/Design:**

Sixty men and women from assisted living communities over 65 years will be recruited from senior retirement facilities and randomized into a group based, pole walking program, or walking program. The pole walking group will use the Exerstrider method of pole walking. Total duration of the programs is 12 weeks, with three sessions per week, building from 20 minute to 30 minute sessions.

The primary outcome is physical function, as measured by items from the Seniors Fitness Test and hand grip strength. Secondary outcomes include, physical activity levels, sedentary behaviour, joint pain, and quality of life. All outcomes will be assessed before and after the programs, using valid and reliable measures.

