### Sample size

There are no previous data on the effects of PW compared with RW on physical function and psychosocial health. Sample size estimates were therefore based on the premise that the PW group would achieve changes at least 20% greater than those observed in the RW group, in selected measures of the Seniors Fitness Test (30-second chair-stand test, 30-second arm-curl test, timed up and go test, and a 6-minute walk test)
[54]. This difference is thought to be a clinically relevant difference in functional status
[52]. Of those subtests, the largest number of participants needed for a stastistically significant 20% difference was for the arm curl test. Based on a 20% difference in normative data for women aged 65–69 years for the arm curl test (mean, 17, SD, 4.1), a power of 0.80 and significance of 0.05, and using the formula n = 2[z*s^2^/Δ^2^], we estimate that 23 participants per group would be needed to detect a between group difference of 20% (i.e. mean, 3, SD, 4.1) in the change score
[52].

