#### Data analysis

To ensure that randomization resulted in equal distribution of sample characteristics in both intervention groups, baseline characteristics in the intervention and control groups will be compared using t-tests for normally distributed continuous data, appropriate non-parametric tests for non-normally distributed continuous data and chi square tests for categorical variables. Between group differences in study outcomes will be examined using repeated measures of covariance (ANCOVA), adjusted for variables that are associated with both the explanatory and outcome measures; based on previous publications, these may include factors such as age, sex and number of medical conditions.

Both intention to treat analysis, including all participants who were enrolled in the study, and provided both baseline and follow up data, and per protocol analyses, including only participants who completed the program, will be analysed. The level of significance will be set at 0.05. All analyses will be conducted using SPSS version 20 (SPSS Inc, Chicago, IL).

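### Five primary outcomes share one unadjusted 0.05 level with no rule joining them; if any one significant result counts, the false-positive chance is about 10–23%, not 5%

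*Protocol article*

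**What the plan says.** The Outcome measures section uses the plural: "The primary outcome measures are selected physical function items of the Seniors Fitness Test", followed by the list "30 second chair stand, 30 second arm curl, timed up and go test, and 6 minute walk test) and grip strength". The section headed Primary outcome measures then describes all five. The abstract uses the singular: "The primary outcome is physical function, as measured by items from the Seniors Fitness Test and hand grip strength".

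On analysis, the Data analysis section says "Between group differences in study outcomes will be examined using repeated measures of covariance (ANCOVA" with covariate adjustment, and "The level of significance will be set at 0.05". It gives no composite, global test, order of testing, required number of successes or adjustment of the level.

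The null hypothesis at the end of the Background is one statement of no difference between the groups, covering physical function, activity and sitting time, and wellbeing together.

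The Sample size section considers the four Seniors Fitness Test items and reports that "the largest number of participants needed for a stastistically significant 20% difference was for the arm curl test". It arrives at 23 per group with "a power of 0.80 and significance of 0.05". Grip strength is not among the items considered. The Randomization section plans about 30 per group.

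**The concern.** The aim is to compare the two programs on physical function, and five separate measurements carry that claim. One null hypothesis covers them all, one 0.05 level is given, and nothing says how the five results combine into a conclusion. A reader of the final report could treat a significant result on any one measure as showing a difference in physical function. Nothing in the article excludes that, and a single significant result does contradict the null as it is worded.

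Used in that way, the 5% level holds for each test but not for the claim. What is at stake is whether the trial's main conclusion has a controlled error rate. A related gap is that the sample size was set for single tests at the full 0.05, so there is no stated power for any rule that controls the error across all five.

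**Working it through.** **Inputs from the article.** Five primary outcomes (Outcome measures). Level 0.05 (Data analysis and Sample size). Power 0.80, and "normative data for women aged 65–69 years for the arm curl test (mean, 17, SD, 4.1" (Sample size); 20% of 17 is 3.4, but the difference printed there is 3. Stated n is 23 per group; planned enrolment is about 30 per group (Randomization).

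**Inputs assumed.** Two-sided tests, since the article does not state sidedness. A common correlation rho between the five test statistics, varied because the article gives none.

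**Step 1: reproduce the stated sample size.** n per group = 2(z₀.₉₇₅ + z₀.₈₀)²·SD²/Δ².
- Δ = 3.4: 2 × (1.960 + 0.842)² × 4.1² / 3.4² = 22.8, so 23. This matches.
- Δ = 3: the same formula gives 29.3, so 30. This does not match two-sided. A one-sided test with Δ = 3 gives 23.1, so 24.

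The stated 23 is therefore what a single two-sided test at an unadjusted 0.05 needs for a difference of 3.4. The calculation makes no allowance for several primaries.

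**Step 2: chance of at least one false positive in five tests at 0.05, when no outcome truly differs.** If independent: 1 − 0.95⁵ = 0.226. If equicorrelated, this is the multivariate normal probability that at least one |Z| exceeds 1.96, found by numerical integration:

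| Assumed rho | At least one false positive |
|---|---|
| 0 | 22.6% |
| 0.3 | 20.9% |
| 0.5 | 18.3% |
| 0.7 | 14.8% |
| 0.8 | 12.7% |
| 0.9 | 10.2% |

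Simulated t-tests with 30 per group agree: 22.5%, 20.8%, 18.5% and 15.0% at rho 0, 0.3, 0.5 and 0.7. Relative to 5%, the inflation runs from 10.2/5 = 2.0 times to 22.6/5 = 4.5 times.

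**Step 3: the same probability with the level split.** At 0.05/5 = 0.01 per test: 1 − 0.99⁵ = 4.9% if independent, and 3.5% at rho 0.7. Holm starts at 0.01 for the smallest p-value, so when none of the five outcomes differs its error rate equals these figures.

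**Step 4: what this costs in power for arm curl.** Two-sided t-test at 0.01, SD 4.1:

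| Difference | 23 per group | 30 per group |
|---|---|---|
| 3.4 | 55% | 71% |
| 3 | 43% | 57% |

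These are lower bounds under Holm. The 0.01 threshold applies only to the smallest p-value, and later steps use 0.0125, 0.0167, 0.025 and 0.05. By the normal approximation used in Step 1, 80% power at 0.01 needs 34 per group for 3.4 and 44 per group for 3.

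**The case against.** The strongest reply is that this is silence rather than error. A condensed article often leaves the handling of several primaries to an analysis plan, and a single stated level does not say that each test is run unadjusted. That is fair as far as it goes: testing each of the five at 0.05 is inferred from the text, not stated in it. But the article itself fixes five primaries, one joint null and one level, sizes the trial on single tests at that level, and describes the primary outcome as one thing in the abstract and as five measures in the methods. Which results decide the trial is a design choice, and these statements leave it open.

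The second reply is that no section says any one significant result is enough. This also stands. If all five had to be significant, there would be no inflation, and sizing on the most demanding of the four fitness items is compatible with wanting each item powered in its own right. A reader might infer that the trial as designed has a 15–23% false-positive rate, or three to four times the nominal level. The article does not support so firm a statement. The figure depends on the any-one reading, and a floor of 15% depends on choosing a correlation near 0.7. Higher correlations bring it down to about 10%, though still to twice 5%.

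A reader might also infer that arm curl is the natural sole primary. The Sample size section singles it out only because it needed the most participants. The aim is physical function overall, and the Discussion stresses daily living, falls and independence. Reducing that to one upper-limb test would narrow the question, and demoting four primaries in a registered, ethics-approved trial is more than a change of wording.

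The absence of grip strength from the sample size is a point about power. It adds nothing to the false-positive argument.

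**Conclusion.** The concern holds in conditional form. The article names five primary outcomes under a single 0.05 level, with neither an adjustment nor a joint rule, so it does not secure 5% error control for the physical-function claim. If any one significant primary result counts against the null, the error is 22.6% under independence and about 10–21% for common correlations from 0.9 down to 0.3, or roughly two to four and a half times the nominal level.

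This rests on three assumptions: each outcome is tested two-sided at 0.05, one success suffices, and the correlations lie in the assumed range. Inflation is present at every correlation examined; only its size is uncertain. The figures do not count the further chances that arise from running both intention-to-treat and per-protocol analyses.

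**What to change.** Keep the five primary outcomes and state that they are tested by Holm's procedure at an overall two-sided 0.05. Word the abstract and the Outcome measures section alike, so that both show how five results lead to one conclusion.

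Restate the power under that rule. Say whether the target arm-curl difference is 3.4 or 3, and include grip strength, which the present calculation omits.

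The cost is lower guaranteed power per test. At about 30 per group, the guaranteed arm-curl power is 71% for a difference of 3.4 or 57% for 3, against the 80% planned for a single test at 0.05. Either the lower figure is accepted and reported, or enrolment rises.

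The alternative is to name one primary outcome before the data are seen and make the other four secondary. That keeps the full 0.05 for the chosen outcome. Arm curl is one candidate because the sample size rests on it, but the choice belongs to the investigators. It would change the trial's primary outcome and narrow the question.

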### Primary outcome measures

#### Senior fitness test

The Senior Fitness Test is used to assess physical function, according to standard protocols
[54]. This is a widely used test battery for evaluating the effect of exercise interventions in older adults, with 6 subtests which measure the physical abilities needed to perform activities of daily living. However, two of the subtests, for upper and lower limb flexibility, will not be used, as flexibility is not an outcome of interest in this study. Therefore, the tests used in this trial will be: 30-second chair-stand test (the number of times in 30 seconds a participant can stand fully from a seated position without using their arms); 30-second arm-curl test (the number of times a 2.27 kg (5 lb) weight can be curled fully on the dominant side); 2.44 m (8 ft) timed up and go test (the time in which participants can stand from a chair, walk 2.44 m, then return and sit down); and the 6-minute walk test (the maximum distance a participant can in six minutes)
[56]. All tests will be measured once, except the timed up and go test, which will consist of a practice, then two trials. The Seniors Fitness Test has acceptable test-retest reliability (R = 0.81-0.98), construct validity against a range of indicators, such as age and exercise status, and criterion validity (r = 0.71-0.82)
[54].

#### Hand grip strength test

Hand grip strength is associated with functional limitations, premature mortality, and the development of disability in older adults
[57]. Hand grip strength will be measured by the amount of static force that the participant’s dominant hand can squeeze around a dynamometer. A Jamar dynamometer will be used as it is accurate, and shows good inter-rater and test-retest reliability and validity in the older adult population
[58,59]. Hand grip strength will be measured in the seated position as per the standard testing protocol approved by the American Society of Hand Therapists (ASHT)
[60]. Three trials of grip strength for each hand, with a 60 second rest period between trials, and each with a three second maximum grip, will be conducted and the maximum value recorded
[61].

### Secondary outcome measures

#### Behaviour

**Objectively measured PA and sitting time** A tri-axial accelerometer (ActiGraph GT3X+) will be used to assess levels of physical activity and sedentary behaviour in all participants in both the PW and the RW groups before, during (week 6), and at the end of the program (week 12). Participants will be shown by the lead researcher how to position the actigraph accelerometer, which will be worn on an elastic clip-on belt, above the left iliac crest. Participants will be asked to put it on when they first get up in the morning and wear it until going to bed at night. In addition, participants will be asked to complete an activity diary to verify the time that the accelerometer was worn. Valid wear time will be defined as a minimum wear time of 10 hours per day for 4 days
[62,63]. Sedentary behaviour will be defined as < 200 cpm, light intensity activity as 200–2689 cpm, moderate intensity activity as 2690–6166 cpm, and vigorous intensity activity as > 6167 cpm
[64,65].

##### 

**Self reported PA** The Active Australia Survey is a self-administered survey which is widely used to assess PA in Australian national and state surveys, and intervention studies
[66]. Items have acceptable measurement properties for ambulatory older adults
[67]. It consists of a set of questions which assess frequency and total time spent walking, and in moderate and vigorous leisure time activity in the past week. Time in each activity is multiplied by a generic metabolic equivalent value of 3.33 METs for walking and moderate activity, and 6.66 METs for vigorous activity, and the sum of all MET.minutes per week is categorized as no PA, (< 33), some PA (33–499), or meeting PA guidelines (≥ 500-999), or high PA (≥ 1000).

##### 

**Self-reported sitting time** Sitting time will be assessed by a five domain sitting questionnaire
[68]. The questionnaire assesses the number of hours spent sitting at work, while travelling, watching television, and using a computer when not at work, and during other recreation. These domain specific questions have acceptable reliability and validity
[68].

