## Background

Being physically active is associated with better physical and mental health in adults, and it is well documented that there is no age limit to health benefits related to regular physical activity (PA)
[1]. Regular PA leads to improvements in cardiorespiratory fitness, muscle strength, endurance and flexibility
[2]. It is also associated with a decrease in the overall burden of disease, as well as improvements in psychological wellbeing, quality of life and cognitive functioning
[2,3]. In older adults, there is now good evidence that regular PA increases average life expectancy and reduces disability
[4,5]. PA which incorporates specific strength, flexibility and balance training, is also associated with a reduction in the risk of falls in this age group
[6,7].

Australian PA guidelines for older adults recommend accumulation of at least two and one half hours of moderate intensity PA on most, preferably all, days of the week for health benefits
[8]. US guidelines for older adults add that some PA is better than none, and that older adults who participate in any amount of PA will gain health benefits
[5,9]. However, PA participation among older adults is low
[10-12]. For example, of Australians aged 65–74 years, only one in three met PA guidelines in 2007–8, and the proportion was just over one in five in those over 75 years
[13]. The proportion of adults aged over 65 years is expected to increase from 13% of the total Australian population in 2007 to between 23% and 25% in 2056
[10]. Consequently, there will be a significant increase in the number of older adults who could potentially obtain health benefits from regular participation in PA. It is therefore important to find feasible ways for older adults to increase their PA levels.

Walking is one PA option for older adults, as it can be undertaken regardless of age, health status, and ability
[14,15]. It is the most frequently reported form of PA in this population group
[16,17]. For example, data from the US Behavioural Risk Factor Surveillance System (BRFSS) show that 44% of men, and 45% of women, aged over 65 years, reported leisure time walking in 2000
[18]. In addition, walking is the most frequently reported activity among older adults who meet the US PA guidelines/recommendations
[18]. In Australia, walking for leisure is reported by 46% of adults over 65 years, and of those, 53% engage exclusively in walking

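### The truncated MET weights do not fit the self-reported activity bands: exactly 150 moderate-equivalent minutes a week scores 499.5 and is not credited as meeting the guideline

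*Protocol article*

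**What the plan says.** In the protocol article, under Secondary outcome measures, Behaviour (Self reported PA), the survey records "frequency and total time spent walking, and in moderate and vigorous leisure time activity in the past week". The scoring rule is "Time in each activity is multiplied by a generic metabolic equivalent value of 3.33 METs for walking and moderate activity". Vigorous time carries twice that weight, given as "6.66 METs for vigorous activity". The weekly total is then "categorized as no PA, (< 33), some PA (33–499), or meeting PA guidelines (≥ 500-999), or high PA (≥ 1000"). No rounding rule is given.

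The Background gives the national guideline for older adults as "accumulation of at least two and one half hours of moderate intensity PA on most, preferably all, days of the week".

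Under Data analysis, the only between-group method named for outcomes is: "Between group differences in study outcomes will be examined using repeated measures of covariance (ANCOVA"). Chi-square tests appear there only for the comparison of baseline characteristics.

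**The concern.** A band labelled as meeting the guideline should contain the person who does exactly the guideline amount. With the printed weights it does not: that person lands in a gap between two bands, or below the threshold if the 500 rule is applied strictly.

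The value is not an odd one. Self-reported durations tend to be round numbers, and 150 minutes is five walks of 30 minutes, the session length the programme builds up to. With about 30 participants per arm, each person placed on the wrong side moves that arm's proportion meeting the guideline by 1/30, or 3.3 percentage points.

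A second, smaller matter follows. The outcome is described as ending in four ordered categories, while the only named outcome model suits a continuous variable. The text does not say which form is analysed.

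**Working it through.** **Inputs**
- Weights 3.33 (walking and moderate) and 6.66 (vigorous): Behaviour, Self reported PA.
- Lower bounds 33, 500 and 1000 MET.min per week, in whole numbers: same place.
- Guideline amount of two and a half hours, 150 minutes: Background. Treating it as a weekly total is a reading, because the sentence does not say so outright. The survey's one-week recall and step 1 support it.
- About 30 participants per arm: Randomization.

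**1. Reproduce the stated bound.** 500 / 3.33 = 150.15 minutes, and 150 × 10/3 = 500.0. The 500 bound is therefore 150 minutes a week on a 10/3 scale. The other bounds fit the same scale: 10 × 10/3 = 33.3 and 300 × 10/3 = 1000.

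**2. Apply the printed weights.** Since 6.66 = 2 × 3.33, the score is 3.33 × (M + 2V), where M is walking plus moderate minutes and V is vigorous minutes.

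| Weekly time | Printed weights | With 10/3 and 20/3 |
|---|---|---|
| 10 min moderate | 33.3 | 33.3 |
| 150 min moderate | 499.5 | 500 |
| 75 min vigorous | 499.5 | 500 |
| 90 min moderate + 30 min vigorous | 299.7 + 199.8 = 499.5 | 300 + 200 = 500 |
| 300 min moderate | 999.0 | 1000 |

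Every mix with M + 2V = 150 scores 499.5. That is above 499 and below 500, so it belongs to no stated band. A score of 999.0 falls inside the guideline-met band rather than the highest one.

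**3. Size of the mismatch.** At 150 minutes the shortfall is 500 − 499.5 = 0.5 MET.min, or 0.1%, equivalent to 0.15 minutes (9 seconds) of walking a week. The neighbouring whole-minute totals are unaffected: 149 × 3.33 = 496.17 and 151 × 3.33 = 502.83. Only a total of exactly 150 moderate-equivalent minutes falls in the gap.

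**4. Would rounding repair it?** To the nearest whole number, 499.5 becomes 500 and is credited. But 999.0 stays at 999, so rounding repairs the lower bound and not the upper one. With 10/3, consecutive whole-minute totals are 3.33 apart and 150 and 300 minutes land on 500 and 1000, so neither gap is hit.

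**5. Outcome form against model.** The Behaviour section first forms a continuous weekly sum and then bands it. Data analysis names ANCOVA for study outcomes and no ordinal or categorical outcome method. The two sections do not state which of the two forms enters the model.

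**The case against.** The strongest reply is that nothing is wrong with the threshold. The 500 bound reproduces from 150 minutes, the bands are printed in whole numbers, and 499.5 rounds to 500. On that view only a rounding convention is missing, which a journal article may leave to the full protocol, the analysis plan or the survey's scoring source. The document also does not place 499.5 in the second band, so it does not positively class that person as failing the guideline. The measure is one of several secondary outcomes, sits beside accelerometer data, and is scored identically in both arms.

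Much of this stands. A reader might infer that the 500 cut-off is wrong; it is not, and the fault lies in the truncated weights. A reader might also infer that the proportion meeting the guideline is understated by a material amount. The document gives no frequency of reports at exactly 150 moderate-equivalent minutes, so no such amount can be calculated.

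What does not stand is that rounding settles the matter. The weights and bounds are both printed, they disagree at the value the band is named for, and rounding leaves 300 minutes at 999. That is a stated rule that does not work as written, rather than an omitted detail.

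On the model, a reader might infer that category codes will be put into the ANCOVA. The document does not say so: that comes from joining two sections, and the continuous sum is available. If the sum is analysed, the boundary has no effect on the between-group comparison.

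**Conclusion.** The point holds as a scoring inconsistency of low importance. With the printed weights, 150 minutes of moderate activity, 75 minutes of vigorous activity, or any equivalent mix scores 499.5. Under the literal rule that is not credited as meeting the guideline. 300 minutes scores 999.0 and misses 1000.

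Two assumptions are involved: that the guideline amount is a weekly total, which the 500 bound itself supports, and that 1000 is meant as 300 minutes, which is inferred from the scale and not stated.

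The consequence is confined to the categorical form of one secondary self-report measure. The same rule applies to both arms, so it mainly affects descriptive proportions, and no bias in the comparison of pole walking with regular walking has been shown. The frequency is unknown. Naming the analysed variable is a useful clarification alongside the scoring correction, not evidence of a modelling error.

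**What to change.** - Score with weights of 10/3 and 20/3. Alternatively, define the bands directly by moderate-equivalent minutes (walking plus moderate plus twice vigorous), for example 150 or more for meeting the guideline and, if that is the intention, 300 or more for the highest band. Moving only the 500 bound to 499.5 would leave the upper one uncorrected.
- Name the continuous MET.min per week sum, transformed if skewed, as the variable in the ANCOVA. Show the four categories descriptively or analyse them with an ordinal model.

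The cost is one line of scoring code and one line of analysis wording. Nothing needs to be collected again, because the survey already records the minutes.
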